#### Exclusion Criteria

- 1) History of hypersensitivity to any cannabinoid.
- 2) The presence of an unstable seizure disorder as defined by having not been seizure-free for at least 6 months or anticonvulsant treatment has not been stable for at least 4 weeks.

- 3) The presence of any clinically significant or unstable medical conditions, including cardiovascular, liver, kidney, pulmonary disease, presence of known congenital brain malformation, as per investigator assessment based on medical history and chart review.
- 4) The presence of a lifetime diagnosis of psychotic disorders, bipolar disorder, or substance use disorder, or current diagnosis of major depressive disorder or dementia, based on past psychiatric history noted in the medical chart, as well as Moss-PAS (ID) at S-V.
- 5) Family history of psychotic disorders.
- 6) Change in psychotropic medications less than 4 weeks prior to study drug use.
- 7) At the time of screening, each adult's medication list will be checked for drugs that are known to cause interactions with nabilone. When a given adult is taking any drugs or is taking a given medication exceeding a given dose) in the following list, he/she/they will be excluded.
  - a. Currently on benzodiazepines at the dose more than the benzodiazepine equivalent to lorazepam 2 mg daily.
  - b. Currently on medical psychostimulant, including methylphenidate (100 mg daily), lisdexamfetamine (70 mg daily), amphetamine/dextroamphetamine (Adderall XR®, 50 mg daily), dextroamphetamine (Dexedrine®, 50 mg daily) at the dose exceeding their respective maximum doses (as shown in the bracket after each agent) to treat ADHD in adults, based on the CADDRA guideline, [www.caddra.ca](http://www.caddra.ca).
  - c. Currently on nonbenzodiazepine hypnotics, including zaleplon (10 mg daily), zolpidem (10 mg daily), and zopiclone (7.5 mg daily), at the dose exceeding their respective suggested safety doses (as shown in the bracket after each agent), based on Canadian Recalls and Safety Alerts (<https://healthycanadians.gc.ca/recall-alert-rappel-avis/>).
  - d. Currently on any opioids.
  - e. Currently on barbiturates.
  - f. Drinking any alcohol one week before the screening visit.
  - g. Recreational use of any psychomimetic drugs, including Ketamine, LSD, MDMA, Magic mushrooms, PCP, Salvia, GHB, Bath salts, Methamphetamine; the last use happens within one week before the screening visit.
- 8) Adults currently taking other cannabinoids, such as CBD or medical cannabis, from another source, unless participants and/or their caregivers are willing to stop this treatment for at least 4 weeks prior to entering the study.
- 9) Adults who might travel out of the area for a significant time during the study.
- 10) Adults who recently are participating in another investigational drug trial.
- 11) Pregnancy.
- 12) Sexually active women of child-bearing potential intended to give breastfeeding or to get pregnant.

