shipment inventory. Any damaged or unusable nabilone in a given pick-up will be documented in the clinical trial files. Regarding dispensing the study medication, participants/caregivers will come to CAMH at 3 separate times to pick up nabilone (Table 1), including 1) to pick up the package for the whole dose titration phase and the first 6 days of the stable dose phase at the Pre-treatment Visit (V 0), 2) to pick up the package for the remaining days of the stable phase, and 3) to pick up the package for the dose tapering phase at the Post-treatment Visit (V 1). Nabilone will be prepared for each visit by Research Pharmacy Service. Participants/caregivers will be requested to document the details of using nabilone and other concomitant medications in the drug diary. They will also be asked and expected to return the empty or any leftover nabilone back to the study team, to help with drug accountability.

Regular study intervention reconciliation will be performed to document nabilone assigned, consumed, and remaining. This reconciliation will be logged on a drug accountability log, and signed and dated by delegated research and/or pharmacy staff.

At the completion of the clinical trial, there will be a final reconciliation of the nabilone dispensed, consumed and remaining, based on the drug diary, the remaining drugs which are returned. This reconciliation will be logged on an accountability form, and signed and dated by delegated research and/or pharmacy staff. Any discrepancies noted will be investigated, resolved, and documented prior to return or destruction of unused study intervention. Intervention destroyed on site will be documented in the clinical trial's files.

All participants entering the dose titration phase will be included in the description of the safety profile and tolerability of nabilone (the Primary Objective). Participants completing the dose titration stage will be included in the final statistical analysis for the Exploratory Objective (i.e., explore changes in SBP in participants pre-and post-treatment), regardless of whether they complete the full protocol. This approach is consistent with the intention-to-treat principle.

**Figure 1.** A schematic diagram of the study procedures, including all study visits and timelines. Abbreviation: S-V: a screening visit; V 0: a baseline visit; V 1: a visit at the end of open label phase; V-F: a follow-up visit to ensure safety; d: days; wk: weeks; FU: follow-up; max: maximum.

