### 3.2. Assessments and visits (Table 1):

Screening assessments for participants and their caregivers include:

- Assessment of prior medical records to collect information of previous cognitive assessment regarding IQ, status of Disability of Ontario Services (DSO), co-occurring physical and psychiatric diagnoses, medication use and potential changes.
- Assessment of capacity to make an informed consent based on both the MacArthur Competence Assessment Tool for Clinical Research (MacCAT-CR) (44) and clinical assessment (45). This will be carried out before the informed consent process and formal assessment.
- Interview of the Moss Psychiatric Assessment Schedules (Moss-PAS (ID)) to the caregiver to assess for co-occurring mental health conditions.
- The Adaptive Behavior Assessment System, Third Edition (ABAS-3), Adult Form, will measure adaptive behaviour and function.
- Measuring of vital signs, weight and height.
- Urine pregnancy test for sexually active women of child-bearing potential.
- Caregiver rated Aberrant Behavior Checklist-Irritability subscale (ABC-I) will be used to define the SBP. Clinical Global Impression – Severity scale (CGI-S) will be rated by the investigator to evaluate the severity of the behavioural problems.

Baseline (pre-treatment) assessments include:

- Measuring of vital signs and weight.
- Assessment of participants' cognitive capacity using the NIH Toolbox® Cognition Battery.
- Assessment of SBP of participants using the ABC-I and MOAS, and anxiety using the General Anxiety Subscale of the ADAMS, as reported by the caregivers.
- Assessment of caregiver's stress and crisis using the Stress Subscale of DASS-21 and BFDS.
- Exploratory assessment of autism symptoms using the Social Communication Questionnaire for Adults with Intellectual Disability (SCQ-AID).

- Optional assessment of MRI Imaging (dependent on the participant's ability to comply with the following assessments, in the opinion of the carers/parents and investigator).
- Concomitant medication

Post-treatment assessments include:

- Assessment of adverse events using the UKU side effect rating scale, examined by the researcher or investigator.
- Re-measuring of vital signs and weight.
- Re-assessment of participants' cognitive capacity using the NIH Toolbox® Cognition Battery.

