### Elective Virtual Assessment

To reduce barriers associated with traffic and time and to future-proof the research protocol in case of another COVID lockdown, we will provide the option for virtual assessments. As shown in the last column of Table 1, interviews that collect data on demographics, clinical history, diagnoses alongside medication use, competence, and adverse effects can be conducted virtually using teleconferencing/videoconferencing software (Webex). Additionally, a blank paper copy of outcome measures rated by caregivers (including the ABC-I, MOAS, Anxiety-ADAMS, Stress-DASS-21, BFDS, and SCQ-AIQ) can be electively sent to them via mail. Completed questionnaires can be mailed, faxed, scanned, or photographed back to the study team. If the caregivers choose to send the completed questionnaire by mail, we will provide a pre-paid postage envelope.

The virtual sessions will be undertaken in coordination with in-person sessions based on the same research standards. The participants and caregivers can flexibly choose either the in-person or virtual assessments for those elective options (Table 1). We will notify both the participant and their caregiver of this virtual option when explaining the study (based on the Telephone Contact Script) and discussing the informed consent.

If the participant/SDM/caregiver chooses to have a virtual informed consent process (as detailed in Section 5) and virtual screening assessment, we will only start the assessment after we receive

the signed informed consent form (with wet signatures). To reduce the barriers by enhancing the convenience and flexibility of participants/caregivers, if they choose to have screening assessments done virtually, the measures of the Screening Visit which require in-person assessments (i.e., pregnancy test, height, vital signs and physical examination) will be carried out in combination with those implemented during the pre-treatment assessment (V 0).

During virtual visits, the study team will document the records of virtual assessment on a study computer and sign the documents with e-signature first when working remotely. Then the person(s) who implements the virtual assessment will then print out the e-signed records and add a wet signature to verify the sources at first available opportunity on-site.

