### **3.3 Selection Criteria**

#### Inclusion Criteria

Participants of any sex or gender, race or ethnicity meeting all criteria listed below will be included in the study:

- 1) Aged  $\geq 25$  years, as medical cannabis should not be used in any person aged  $< 25$  as suggested by Health Canada (24).
- 2) Adults with a DSM-5 diagnosis of ID meeting: a. Full scale IQ  $< 70$  on a standardized cognitive assessment reported in their prior medical record; b. A deficit in adaptive function in at least one activity of life, as estimated by the Adaptive Behavior Assessment System, rated by the caregiver. For those whose verified records are not available, they are deemed eligible if they are connected with Disability Services Ontario. People with ID and other developmental disabilities, e.g., autism, Down syndrome, genetic conditions such as Angelman syndrome, fragile X syndrome, Prader-Willi Syndrome, etc., will also be enrolled.
- 3) SBP, including aggressive, disruptive, and/or self-injurious behaviours in any situation (home, day program, clinic, etc.), defined as a score  $\geq 18$  on the Aberrant Behaviour Checklist-Irritability subscale (ABC-I), and a score  $\geq 4$  on the Clinical Global Impressions-Severity scale (41). A consistent pattern of frequent SBP should occur for  $> 3$  months  $\geq 1$  time per week.
- 4) Sexually active women of child-bearing potential must have a negative urine pregnancy test at the screening visit.
- 5) Sexually active women of child-bearing must use an effective method of birth control at least from the start of last two normal menses before the screening visit to one month after the end of the study (completion of the safety visit). The accepted methods of contraception include total sexual abstinence, if it is the usual and preferred lifestyle, or consistently and correctly taking the oral hormonal contraceptive.
- 6) Adults who receive a blood test in recent 12 months, which shows liver function test with the ALT  $\leq 3$  times the upper limit of normal and bilirubin  $\leq 2$  times the upper limit of normal.
- 7) At least one month that needs to pass from the participation in another investigational drug trial to a given adults being allowed to participate in this trial.

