## **5. CONSENT**

- The research assistant will schedule the first appointment (research screening visit) to discuss the study and obtain written informed consent from the participant or their SDM.
  - The participant or their SDM will be provided with the informed consent form either by email, mail, or secure file transfer (as noted in the Telephone Contact Script) before the consent discussion.

- SDM consent is included as the patient may not have the capacity to make the decision about study participation. As per the Tri-Council Policy Statement: Ethical Conduct for Research Involving Humans, principle of respect for persons implies that those who lack the capacity to make decisions for themselves should have the opportunity to participate in research that may be of benefit to themselves or others. SDMs may decide whether participation in a particular study would be appropriate. These principles involve considerations of concern for welfare and justice.
- Consent will be documented on the written Informed Consent Form (ICF). This will include signatures from the participant/SDM, the person conducting the consent discussion, and the witness (if applicable). Full explanation about this study will be provided to the participants and/or their SDMs.
  - If the consent discussion is conducted in person, the participant/SDM will be provided with a completed and signed copy of the informed consent form at the end of their visit.
- The MacArthur Competence Assessment Tool for Clinical Research (MacCAT-CR) will be applied to both of them as needed in order to ensure that they understand the information presented in the ICF. A score of 70% or higher in the MacCAT-CR will be required to pass.
  - 1) If the participant passes the MacCAT, written informed consent will be obtained from the participant.
  - 2) If the participant is not able to complete or does not pass the MacCAT and their SDM passes the MacCAT, written informed consent will be obtained from the SDM.

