## **8. SAMPLE SIZE AND DATA ANALYSIS**

To test the Hypotheses 1 and 2, we aim to enroll 40 patients to enter the dose titration phase, consistent with common sample sizes for Phase I trials (63).

We assume the attrition rate of 25% from the dose titration phase to entering the open-label phase. To test behavioural changes at the group level (Exploratory Objective), the sample size of the remaining participants (N=30) could be sufficient to detect differences with effect size Cohen's d as low as of 0.53, and at power = 0.8 and two-sided  $\alpha$ -level = 0.05 (G\*Power 3.1), which is similar to that detected in the study investigating the effects of nabilone on agitation associated with dementia (27).

Paired-t test will be used to investigate the pre- vs. post-treatment behavioural and brain changes. Exploratory analyses will be performed to determine predictors of response including baseline individual features, using logistic regression. Safety profiles will be described in the percentage of each adverse effects. For MRI measures, non-parametric tests will be used to explore the brain changes with nabilone treatment, assuming that only few participants can finish MRI scans eventually.

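### The only breastfeeding criterion is limited to sexually active women of child-bearing potential, so a breastfeeding woman who is not sexually active is eligible as written

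*Protocol*

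**What the plan says.** Protocol Section 3.3 has two exclusions on this subject. Exclusion 11 bars pregnancy and carries no qualifier. Exclusion 12 bars "Sexually active women of child-bearing potential intended to give breastfeeding or to get pregnant". Breastfeeding is mentioned nowhere else in the protocol.

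The pregnancy test has a limit of its own. Inclusion criterion 4 reads "Sexually active women of child-bearing potential must have a negative urine pregnancy test at the screening visit", and the screening list in Section 3.2 repeats this as "Urine pregnancy test for sexually active women of child-bearing potential".

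Inclusion criterion 5 requires contraception of sexually active women and adds: "The accepted methods of contraception include total sexual abstinence, if it is the usual and preferred lifestyle".

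Section 7.1 gives becoming pregnant after the start of the trial as an example of a reason for withdrawal. It does not mention breastfeeding. Section 3.1 places the first hand-out of nabilone at V 0.

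**The concern.** A breastfeeding criterion protects the nursing infant. Whether the infant is exposed depends on whether the woman takes the drug and breastfeeds, and sexual activity does not enter into it. The qualifier is meaningful for contraception and can be defended for pregnancy testing. Carried over to breastfeeding, it removes part of the group the criterion is there to exclude.

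At stake is a safeguard that the sponsor evidently meant to have. The protocol chose to treat breastfeeding as a reason not to give nabilone, and the wording falls short of that choice. The person left unprotected would be an infant, who is not a trial participant.

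**Working it through.** No arithmetic applies, because the point concerns the reach of eligibility criteria. The check is to apply each relevant criterion literally to the possible cases.

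**Criteria used:** inclusions 4 and 5 and exclusions 3, 11 and 12, all in Section 3.3.

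| Case | Inclusions 4 and 5 | Exclusion 11 (pregnancy) | Exclusion 12 (breastfeeding) | Result |
|---|---|---|---|---|
| A. Breastfeeding and means to continue, sexually active, of child-bearing potential | Apply | Not met | Met on a reasonable reading | Excluded |
| B. Breastfeeding, not sexually active | Do not apply | Not met | Opening condition fails | Not excluded on this ground |
| C. Known to be pregnant, whether or not sexually active | Not decisive | Met | Not needed | Excluded |
| D. Pregnancy unrecognised, woman classed as not sexually active | No test required | Applies, but no required test checks it | Opening condition fails | Barred by the rule, possibly undetected |

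**Case B is the finding.** Exclusion 3 does not close it, because that criterion concerns clinically significant or unstable medical conditions and lactation is not one. No other listed criterion mentions breastfeeding. She can be enrolled with every criterion correctly applied.

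**Case A limits the finding.** The criterion is worded as an intention, but a woman who is already breastfeeding and means to continue would reasonably be caught by it. The intention wording is a minor drafting weakness. The gap comes from the sexual-activity condition.

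**Cases C and D separate eligibility from detection.** For pregnancy the eligibility rule is complete, since exclusion 11 applies to everyone. What is narrower is the required test. A pregnancy could pass unnoticed only if a woman were wrongly classed as not sexually active.

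**Size.** Section 8 says "we aim to enroll 40 patients to enter the dose titration phase". The documents give no sex split, no share of women of child-bearing potential and no figure for breastfeeding, so the number of women in case B cannot be calculated. Participants are aged 25 or over with intellectual disability and severe behavioural problems, so the number is likely very small.

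**The case against.** **The phrase may be used loosely.** Inclusion 5 addresses sexually active women yet accepts total abstinence as contraception. If the phrase covers abstinent women there, it may do so in exclusion 12, and the uncovered group would be small or empty. This argument has some force, but it does not settle the matter. An eligibility criterion should not depend on a charitable reading, and on the plain reading the woman in case B is let in.

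**The case is rare, and clinicians would step in.** It probably is rare. Section 7.1 also lets the investigators discontinue any participant in her best interest. That is discretion after enrolment, however, and it does not replace an eligibility rule.

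**The protocol states no lactation risk.** This is correct. Section 9.3 lists adverse effects in people who take nabilone and says nothing about infants, so the size of any harm cannot be judged from the documents. The point rests only on the protocol's own decision to have a breastfeeding criterion.

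Some stronger readings are tempting, and the documents do not support them:

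- *A reader might infer that pregnant women can be enrolled.* They cannot. Exclusion 11 bars pregnancy without condition.
- *A reader might infer that limiting the pregnancy test is an error.* Testing only women reported to be sexually active is a defensible choice. It fails only through misclassification, and nothing in the documents shows that this occurs. Section 5 says "SDM consent is included as the patient may not have the capacity to make the decision about study participation". That concerns capacity to consent and does not say that reports of sexual history are unreliable.
- *A reader might infer that the protocol contradicts itself about who is tested.* Table 1 has a pregnancy row with no stated population, and the Elective Virtual Assessment text lists "pregnancy test, height, vital signs and physical examination" among the in-person measures. Both are shorthand for the test defined in Section 3.2 and do not conflict with it.

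**Conclusion.** The concern holds for breastfeeding. Exclusion 12 carries a condition unrelated to what it is meant to prevent, so a breastfeeding woman who is not sexually active is eligible for nabilone as the protocol is written. This assumes that sexually active is read in its ordinary sense. It also assumes that no other part of the protocol governs the matter, and none was found. Consent pages are not available for this review, but a mention there would not alter the criteria in Section 3.3.

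The pregnancy test is a secondary matter. Exclusion 11 is broader than the testing that supports it, so a wider offer of the test is a sensible safeguard, not the correction of a mistake.

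The practical size is likely very small and cannot be put as a number. No endpoint, analysis or statistical result is affected. The change is still worth making, because this is a first study of the drug in this population with safety as its primary objective, and the correction costs almost nothing.

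**What to change.** **Main change.** Reword exclusion 12 to exclude any woman who is breastfeeding, or who intends to breastfeed or become pregnant during the study. This removes the condition and covers current breastfeeding explicitly. It changes one line and adds no procedure.

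**Optional safeguard.** Offer the existing urine pregnancy test to all women of child-bearing potential before nabilone is first dispensed at V 0. This also fits the virtual screening option, under which the test is already done together with V 0. The cost is a few more urine tests, which some participants or families may consider unnecessary. If a negative result were made mandatory for these women, some who cannot provide a sample might become ineligible. Offering the test without making its result a condition of entry avoids that loss.

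The contraception requirement in inclusion 5 can stay limited to sexually active women.

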### 3.4 Assessment/Scales/Measures

#### Assessment for Diagnosis

The Moss Psychiatric Assessment Schedules (The Moss-PAS (ID)): The Moss-PAS (ID) (previously called Mini PAS-ADD) (46) provides a wide-spectrum mental health assessment primarily designed for people with intellectual disabilities who have limited language or reduced cognitive development. This semi-structured diagnostic interview, delivered by the PI, is fully compliant with DSM-5 and ICD-11. It consists of 86 items on a 4-point scale: 0 (symptom not present)—3 (symptom is severe). The interview is divided into seven subscales: Depression,

Anxiety, Obsessive Compulsive Disorder, Mania, Psychosis, Unspecified disorder, and Autism. Approximately 30 min to complete.

